### Quality control

Quality control will be carried out under the supervision of the independent steering committee to eliminate potential bias and ensure the quality of the trial. Steering committee consists of investigators with expertise in Tai Chi clinical trials, statistical design, exercise, and adverse events. They are responsible for monitoring data, identifying problems, reviewing collected data, and controlling bias. To ensure consistency in delivery, the protocol will remain the same throughout the 12-week training period. All instructors and assessors must receive standard training prior to the commencement of the trial. The Tai Chi instructor with extensive experience will be required to receive standard training sessions by a nationally recognized academic specialist with more than 20 years of Tai Chi training prior to the initiation of this trial. Training sessions should be conducted in strict accordance with the Tai Chi protocol, including Tai Chi forms, Tai Chi principles, breathing techniques, concentration, and KOA precautions. Both groups will be conducted simultaneously in small groups with at least 9 participants per class to avoid varying severity of KOA depending on the seasons and weather. For participants, they must upload photos or videos of home exercises to provide feedback to instructors and are encouraged to complete their daily punches on a WeChat mini-app. No additional exercises will be assigned to them during the study period. To maintain consistency in individual Tai Chi intensity, all participants will be required to exercise at a moderate intensity of 50-70% of maximum heart rate (calculated as 220-age, beats/minute) for 60 min. In this study, both heart rate and activity intensity will be recorded using Actigraph wGT3X-BT (ActiGraph LLC, Pensacola, FL), which will be worn on the patient’s waists during Tai Chi at the 1st, 6th and 12th intervention. To ensure pre-specified exercise intensity, participants will be trained to wear Actigraph before exercise to measure intensity. If necessary, the Tai Chi instructor will adjust the number and range of movements to achieve the pre-specified intensity. As for pain-relieving medications, participants will be allowed to continue their routine medications to alleviate pain. Any changes in dosage should be recorded in CRFs, but changes to the medical regimen will not be recommended by researchers.

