### Sample size calculation

The calculation of sample size is based on hypothetical changes in WOMAC pain subscale at week 12. We are using the results of a randomized controlled trial [26] to formulate expected effects. We hypothesized that a 118-point improvement in WOMAC pain subscale occurred in the Tai Chi group compared to the attention control group. A sample size of 40 per group provides 90% power to detect these differences using a 2-sided significance level of 0.05 through PASS software (version 15.0.5) and considering the expected dropout rate of 20%, the study will require 100 patients in total.

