### Randomization and allocation concealment

Recruited participants will begin intervention within 1 week of baseline assessment. An independent statistician will use SPSS (version 26.0) to generate the random sequence with a random block size of 2–6. Eligible participants will be randomly assigned to either the TC group or the control group on a 1:1 ratio. Random numbers and assigned groups will be sealed in opaque envelopes, which will be numbered sequentially. The envelopes will not be delivered and opened by a study coordinator until written consent forms and baseline assessments have been completed. The study coordinator will then inform eligible participants of their group allocation and schedule of training sessions by telephone. This trial will be conducted in five cycles of at least 18 participants per cycle for a 12-week intervention course, to ensure a consistent environment for interventions and to maintain an equal number of participants in each group.

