#### Data collection and statistical analysis

A standardized CRF has already been designed prior to the study, including participants’ characteristics, outcome measures, evaluation time points, adverse events, etc. Two independent data administrators, who are blind to group allocation, will check CRF data and double-enter it into an Excel database once a week. Raw data can be shared by contacting researchers if requested within 6 months of completion of the trial.

A complete analysis set (FAS) is based on the ITT principle, which includes all qualified participants who have received at least one intervention and at least one outcome measurement. Missing data will be imputed through last observation carried forward (LOCF) methodology. A Per-Protocol Set (PPS) will also be used to analyze those who completed the trial without major protocol violations as an auxiliary set. The analysis will be based on the intention-to-treat principle and include all randomly assigned participants receiving interventions. Statistical analysis will be carried out by an independent statistician using SPSS version 26.0. Descriptive characteristics will be presented as mean ± standard deviation or median (interquartile range, IQR) for continuous variables and n (%) for categorical variables. Analysis of variance (ANOVA) or Chi-square test will be used to verify baseline balances of variable characteristics between groups, as appropriate. Changes in repeat outcomes over time will be compared by linear-mixed effects model with group and visits as fixed effects. A Bonferroni correction will be used for multiple comparisons. Statistical significance will be set at a 2-tailed p-value of 0.05.

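### Both arms are taught in small classes, but neither the stated power nor the stated model allows for class; if outcomes cluster by class within arm, p-values will be too small and 90% power may not be reached

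*Protocol article*

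**What the plan says.** Participants are randomised individually, 1:1 (protocol article, Randomization and allocation concealment). That section adds: "This trial will be conducted in five cycles of at least 18 participants per cycle for a 12-week intervention course". The Interventions section gives each arm one 60-minute session a week for 12 weeks. The Quality control section says how the sessions are organised: "Both groups will be conducted simultaneously in small groups with at least 9 participants per class to avoid varying severity of KOA". The number of classes is not stated.

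The Sample size calculation section reads: "We hypothesized that a 118-point improvement in WOMAC pain subscale occurred in the Tai Chi group compared to the attention control group", and then "A sample size of 40 per group provides 90% power to detect these differences using a 2-sided significance level of 0.05". It inflates for dropout only: "considering the expected dropout rate of 20%, the study will require 100 patients in total". It gives no SD, within-class correlation or design effect.

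The Data collection and statistical analysis section compares repeated outcomes with a "linear-mixed effects model with group and visits as fixed effects". It names no class, cycle or instructor term and does not describe the random part of the model.

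**The concern.** People taught together for 12 weeks share an instructor, a peer group and the same sessions. The Quality control section also lets the Tai Chi instructor change the number and range of movements to reach the target intensity, so delivery can differ between classes. The primary outcome is self-reported pain, which group experience could plausibly influence. Any of these could make outcomes within a class positively correlated.

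Each class belongs to one arm, so between-class variation adds to the variance of the arm difference. A model without a class term does not count that variation. Its standard error is then too small, its p-values are too small, and a power figure based on independent participants is too high. A participant-level random effect, if one is intended, handles repeated visits and not class membership. What is at stake is whether a borderline positive primary result could be told apart from class effects. A class term added after unblinding would look post hoc.

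**Working it through.** **Inputs from the protocol article.** Difference 118 points; 40 evaluable per group; power 90%; two-sided alpha 0.05; dropout 20%; total 100; five cycles of at least 18; at least 9 per class.

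**Inputs assumed, because not stated.** One class per arm per cycle; class ICC from 0 to 0.10; SD back-solved from the plan's own power.

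**1. The plan's own figures.** Dropout: 80 / (1 − 0.20) = 100, which reproduces exactly. Dropout therefore accounts for the whole step from 80 to 100. The 40 per group cannot be reproduced without an SD. Solving for it:
- t test, 78 df: noncentrality = 118 / (SD × √(2/40)). Power is 90% at SD ≈ 160.8, where the noncentrality is 3.282 and the standardised difference is 118/160.8 ≈ 0.734.
- Normal approximation: SD = 118 × √(40/2) / (1.960 + 1.282) ≈ 163.

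So the stated figure matches an ordinary comparison of independent participants if the SD is about 161 to 163.

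**2. Classes.** 5 cycles × 2 arms = 10 classes. 100/10 = 10 enrolled per class, and 10 × 0.8 = 8 completers.

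**3. Effect of arm-specific class correlation.**
- Design effect: DE = 1 + (8 − 1) × ICC.
- Type I error of the unclustered test: 2 × [1 − Φ(1.96/√DE)]. This does not depend on the SD.
- Power with a correct standard error: noncentral t with noncentrality 3.282/√DE. Example at ICC 0.05: DE = 1.35, and 3.282/1.162 ≈ 2.825.
- Degrees of freedom: 78 means no small-sample correction. Class random without cycle leaves 10 − 2 = 8. Cycle fixed and class random leaves 10 − 1 − 4 − 1 = 4. The critical t values are 1.99, 2.31 and 2.78.

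| ICC | DE | Type I error, unclustered | Power, 78 df | Power, 8 df | Power, 4 df |
|---|---|---|---|---|---|
| 0 | 1.00 | 5.0% | 90.0% | 81.9% | 69.3% |
| 0.01 | 1.07 | 5.8% | 88.0% | 79.3% | 66.5% |
| 0.02 | 1.14 | 6.6% | 85.9% | 76.8% | 63.9% |
| 0.05 | 1.35 | 9.2% | 79.7% | 69.7% | 57.1% |
| 0.10 | 1.70 | 13.3% | 70.1% | 59.9% | 48.2% |

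Simulation (5 + 5 classes of 8, 20,000 runs) gives type I errors of 6.1%, 6.6%, 9.2% and 13.2% for ICC 0.01 to 0.10, and class-level power on 8 df of 79.5%, 76.7%, 69.5% and 59.5%. The unclustered test itself rejects in 89%, 89%, 87% and 84% of runs under the alternative. Those rates are partly bought with the inflated type I error, so they are not valid power.

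The 4-df column is somewhat pessimistic. A fixed cycle effect also removes variance, and Satterthwaite df can be higher when the estimated class variance is small.

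**4. Sensitivity to the SD** (ICC 0.05, 78 df): 96% at SD 120, 93% at 130, 89% at 140, 80% at 161, 70% at 180.

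**5. Correlation shared by both arms within a cycle.** The same set-up was simulated with a total ICC of 0.05. Type I error of the unclustered test is about 9% when none of the correlation is shared, about 7% when half is shared, and between 4% and 5% when all of it is shared. The table is therefore the worst case for a given total ICC.

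**The case against.** The strongest case against has four parts.

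First, everything depends on an arm-specific class ICC above zero, and the article gives none. Randomisation is individual and Tai Chi delivery is standardised. Both arms are also asked for 30 minutes of home exercise daily, about 3.5 hours a week against one class hour. The ICC could be small, and at 0.01 the loss is about 2 points of power. This stands, and it makes the point conditional. A reader might infer that the power and p-values are definitely wrong; the documents do not establish that.

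Second, the power loss uses a back-solved SD. At SD 140 and ICC 0.05, power before any df correction is still 89%. This stands for power but not for type I error, which does not involve the SD. Nor can a reader conclude that the trial is underpowered, because the SD is not stated.

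Third, a reader might blame season, since the protocol expects severity to vary with it. But the arms run simultaneously so that season affects both alike. A shared cycle effect largely cancels in the arm contrast, and ignoring it only wastes precision. It is not a cause of inflation.

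Fourth, the article is condensed and an SAP may specify a class effect. The random part of the model is indeed undescribed, so independence between participants is inferred from the terms named, and ten classes is inferred from minimum sizes. That limits certainty but does not remove the point. The article commits to a finished power figure and to named model terms, and neither reflects the class structure that it describes elsewhere.

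**Conclusion.** The point holds in conditional form. The protocol describes class-based delivery in both arms, while its stated power and stated model terms make no allowance for it. For any positive class correlation specific to an arm, the plan as written gives standard errors and p-values that are too small. For an ICC of 0.01 to 0.10, type I error is about 5.8% to 13.3% and power falls from 90% to between about 88% and 70%, before any df correction. This rests on one class per arm per cycle, 8 completers per class, all the correlation being arm-specific and, for power only, an SD of about 161. The effect is small at ICC 0.01 and material from about 0.05. Because the ICC and SD are unknown, this is a should-fix: the omission is clear, its size is not.

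**What to change.** 1. In the primary model, add a random intercept for class in both arms, acting on change from baseline because classes form only after the baseline assessment. Use a small-sample df correction (Satterthwaite or Kenward-Roger) and report the estimated ICC.
2. Decide before unblinding whether cycle enters as a fixed effect. It removes cycle variation shared by the arms but leaves about 4 class-level df instead of about 8. With only ten classes that is a real trade-off.
3. In the Sample size calculation section, state the SD assumed, and restate power as a range over ICC 0 to 0.10 with the df of the chosen model.
4. State the planned number of classes per arm and cycle.

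Enrolment need not change, and class and cycle should be identifiable from allocation and attendance records. The cost is wider intervals and a clearly less favourable stated power. At SD 161 and ICC 0.02, 0.05 and 0.10, it is about 77%, 70% and 60% with 8 df, or 64%, 57% and 48% with 4 df.

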#### Data collection and statistical analysis

A standardized CRF has already been designed prior to the study, including participants’ characteristics, outcome measures, evaluation time points, adverse events, etc. Two independent data administrators, who are blind to group allocation, will check CRF data and double-enter it into an Excel database once a week. Raw data can be shared by contacting researchers if requested within 6 months of completion of the trial.

A complete analysis set (FAS) is based on the ITT principle, which includes all qualified participants who have received at least one intervention and at least one outcome measurement. Missing data will be imputed through last observation carried forward (LOCF) methodology. A Per-Protocol Set (PPS) will also be used to analyze those who completed the trial without major protocol violations as an auxiliary set. The analysis will be based on the intention-to-treat principle and include all randomly assigned participants receiving interventions. Statistical analysis will be carried out by an independent statistician using SPSS version 26.0. Descriptive characteristics will be presented as mean ± standard deviation or median (interquartile range, IQR) for continuous variables and n (%) for categorical variables. Analysis of variance (ANOVA) or Chi-square test will be used to verify baseline balances of variable characteristics between groups, as appropriate. Changes in repeat outcomes over time will be compared by linear-mixed effects model with group and visits as fixed effects. A Bonferroni correction will be used for multiple comparisons. Statistical significance will be set at a 2-tailed p-value of 0.05.

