### Blinding

Due to the nature of the interventions, instructors and participants will not be blind to group allocations. The study coordinator will be responsible for informing participants of randomized results and scheduling interventions. Data managers, statisticians and evaluators will be blinded to the group allocation throughout the entire procedure to minimize the risk of bias.

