### Adherence

At the beginning of the study, a group of people interested in Tai Chi will be selected to volunteer for the trial. Participants have the right to choose whether or not to participate after a thorough understanding of the assigned groups and procedures. Participants will be encouraged and informed of the detailed exercise contents and benefits once a week via WeChat or telephone. Researchers will visit training sessions and regularly review course videos to monitor the veracity of interventions. Their attendance at each session will be recorded in attendance forms by study assistants who are not involved in intervention, evaluation and data analysis. We will track the reasons for missed sessions and the number of missed sessions. In addition, participants will be required to upload photos or videos of home exercises to provide feedback to instructors and will be encouraged to complete their daily punches on a WeChat mini-app. Pre-recorded Tai Chi training videos will be made to prevent participants in TC group from forgetting details while practicing Tai Chi at home.

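### The analysis labelled intention-to-treat leaves out randomised participants who never start, and its two definitions do not match

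*Protocol article*

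**What the plan says.** The section on data collection and statistical analysis describes the main analysis population twice in one paragraph.

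- **FAS sentence.** "A complete analysis set (FAS) is based on the ITT principle", and it is the set "which includes all qualified participants who have received at least one intervention and at least one outcome measurement".
- **ITT sentence.** "The analysis will be based on the intention-to-treat principle and include all randomly assigned participants receiving interventions".

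Between the two stand the missing-data rule ("Missing data will be imputed through last observation carried forward (LOCF) methodology") and a per-protocol set, which is the only set called auxiliary. Neither sentence is tied to the primary comparison, the change in WOMAC pain from baseline to week 12.

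Other sections bear on who might fail to start. Under randomization and allocation concealment, envelopes are opened only after consent and baseline assessment, and then: "The study coordinator will then inform eligible participants of their group allocation and schedule of training sessions by telephone". Under blinding, "instructors and participants will not be blind to group allocations", whereas "Data managers, statisticians and evaluators will be blinded to the group allocation throughout the entire procedure". The adherence section says that volunteers are sought among people with an interest in Tai Chi.

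**The concern.** Intention-to-treat means that everyone randomised is analysed in the arm assigned. Here a person who is randomised, hears the allocation and never comes to a class leaves the analysis under either sentence. In a double-blind trial this is usually a mild departure, because the decision to start cannot depend on the arm. In this trial it can: the participant knows the arm before the first session, and someone attracted by Tai Chi may have been given lectures and stretching.

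If non-starters differ between arms in number or in kind, the remaining groups are no longer the groups that randomisation formed. The primary outcome is self-reported, and blinding the evaluators does not restore that balance. The report would also claim an intention-to-treat analysis that was not done.

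**Working it through.** **1. The two definitions side by side**

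| Randomised participant | FAS sentence | ITT sentence |
|---|---|---|
| Attends, has follow-up data | in | in |
| Never attends | out | out |
| Attends, no follow-up data | in if a baseline value counts, otherwise out | in |
| Attends, later judged not *qualified* | out, unless the word only means eligible at entry | in |

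The second row is the firm finding: both sentences exclude never-starters. The third and fourth rows show that the definitions can give different sets. Whether they do so in practice depends on two terms that the article leaves open.

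**2. The plan's own figures**

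Inputs from the sample size section: 118-point difference, 40 per group, 90% power, two-sided 0.05, 20% dropout, 100 in total.

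- Total: 80 / (1 − 0.20) = 100, which reproduces.
- No SD is given. Solving back with the normal formula: SD = 118 / [(1.960 + 1.282) × √(2/40)] = 162.8. With the t-test, 40 per group corresponds to an SD of 158.7 to 160.8. I use 161 below.

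**3. Illustration of the possible bias**

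The documents give neither the number who will not start nor how they would differ, so both are assumptions. Let f be the share of an arm that is excluded, and d the difference in *change* in pain between excluded and retained participants, in SDs. Dropping the excluded shifts that arm's mean by f × d × SD. With the same d in both arms:

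bias = (f in control − f in Tai Chi) × d × SD

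The type I error is that of a two-sided normal test at 0.05 with no true effect, centred on bias / SE, where SE = SD × √(1/n₁ + 1/n₂) and n₁, n₂ are the numbers retained.

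| Excluded, control vs Tai Chi (of 50 each) | d | Bias (points) | % of 118 | Type I error |
|---|---|---|---|---|
| 5 vs 0 | 0.5 to 1.0 | 8 to 16 | 7 to 14 | 5.7% to 7.8% |
| 8 vs 2 | 0.5 to 1.0 | 10 to 19 | 8 to 16 | 5.9% to 8.8% |
| 10 vs 0 | 0.5 to 1.0 | 16 to 32 | 14 to 27 | 7.6% to 15.6% |
| 5 vs 5, same kind of person | any | 0 | 0 | 5.0% |

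For the lower end of the 5 vs 0 row: 0.10 × 0.5 × 161 = 8.0 points; SE = 161 × √(1/50 + 1/45) = 33; bias / SE = 0.24; type I error 5.7%.

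Under this formula the bias vanishes if the excluded do not differ from the retained (d = 0), or if equal shares of similar people are lost from both arms. The table puts the loss in the control arm for illustration only.

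**The case against.** Much can be said for the plan.

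- **Outcome measurement.** The FAS sentence does not say post-baseline. All outcomes are taken at baseline, before the envelopes are opened, so read literally this condition may exclude nobody. A reader might infer that people without follow-up are dropped, but the text does not settle it.
- **Qualified.** Screening comes before randomisation, and the article describes no later review of eligibility. The word may simply mean eligible. To read it as licence for exclusions after randomisation is to infer more than is written. Statisticians and data managers are in any case blinded.
- **Consent.** The adherence section says "Participants have the right to choose whether or not to participate after a thorough understanding of the assigned groups and procedures". This could be taken as leave to withdraw once the arm is known, but it stands in a passage about volunteering and may describe ordinary consent before randomisation. The point does not rest on it.
- **Refusal mainly among controls.** This is plausible, given how volunteers are sought, but undocumented. The control programme is meant to sustain attendance, and the intervention starts within a week of baseline. A transport allowance is also paid, though only to those who complete everything, so it gives a non-starter no reason to return for measurement.
- **Size.** Every figure for bias rests on assumed inputs. Ten non-starters in one arm would use up that arm's whole 20% dropout allowance before the first class. Baseline pain is known for everyone, so non-starters can be counted and compared by arm. That is partial evidence, though it cannot show their week-12 change.
- **Drafting.** The ITT sentence can be read as loose shorthand for the FAS sentence.

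These arguments narrow the point. They leave standing that both sentences exclude never-starters under an intention-to-treat label, in a trial where starting follows disclosure of the arm. This is stated text, not detail that an article leaves to an analysis plan.

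**Conclusion.** The point holds in a limited form. The analysis described is a modified intention-to-treat analysis under the wrong name. It is defined twice without agreement, and neither definition is assigned to the primary comparison. Arm-dependent non-starting is possible, because participants know their allocation before the first session and report the primary outcome themselves.

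The size cannot be determined from the documents. With an SD of about 161, equal arms of 50 and the assumed losses above, bias runs from zero to about 32 points, and type I error from 5% to about 16%. The upper end needs 20% of one arm and nobody in the other to be excluded, with a full SD of difference in change. A reader might conclude that the comparison will be biased, or biased in a known direction; the documents support only that it could be. The definition should be fixed, but the material does not show that the trial's conclusion depends on it.

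**What to change.** - Define one primary set for the week-12 comparison: every randomised participant, in the arm assigned, whatever the attendance. Delete the ITT sentence.
- Ask non-starters for the week 6, 12 and 18 questionnaires. The discussion already allows telephone or electronic collection at follow-up. This is the most valuable step, because a baseline value alone says almost nothing about the week-12 contrast.
- Handle those still without follow-up through the mixed model, with multiple imputation as a sensitivity analysis. LOCF would give a participant with only a baseline value a change of zero.
- Keep the present FAS as a supportive set labelled modified intention-to-treat. State whether its outcome measurement must be post-baseline and what *qualified* means.
- Report non-starters by arm, with their baseline pain.

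The cost is a change of wording and a few extra questionnaires. Non-starters may dilute the effect slightly. With outcomes from all 100 and an SD of about 161, power is 95% without dilution, and 93%, 90.5% and 83% if the mean effect falls by 5%, 10% and 20%. If losses reach the planned 20%, the remaining 40 per group have no such reserve. Recruitment has begun, so follow-up of non-starters should start now: a missed week-12 questionnaire cannot be recovered later.

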#### Measures of muscle strength

Maximal voluntary muscle strength of extensor and flexor will be measured by isokinetic dynamometry at angular velocities of 30 deg/s and 60 deg/s (Biodex System 4 Pro, Biodex Medical System, NY, USA) at baseline and week 12. Before the test, the patient will be comfortably positioned on dynamometry with the hip at 85 deg and the knee at 90 deg flexion. The shin will be placed and strapped in the foot adapter and the rotation axis will be aligned with the flexion and extension axis of the knee. The patient will then be instructed to perform flexion and extension according to his or her physiological capability within the range of motion (ROM) of the knee joint during a 5-minute warm-up period to familiarize himself with the test procedure. A gravitational correction will be applied to negate the influence of the gravity-effect torque on the test data. During the formal test, each patient will be required to fold their arms across their chest and given verbal encouragement in an attempt to achieve a maximum level of effort. The angular velocities of 30 deg/s and 60 deg/s will be applied to two sets of five maximal knee extensions and flexions with a 60-second rest interval between sets, which are chosen according to previous studies [22, 35]. The mean of each set will be selected as maximal isokinetic muscle strength. The peak torque (PT), peak work (PW), total work (TW), peak torque angle (PTA) and average power (AP) of quadriceps were recorded for each velocity.

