While the purpose of this trial is to address the limitations of previous trials, potential challenges remain to be addressed. First, to ensure the successful implementation of the protocol, all researchers are trained prior to the start of the trial and are prepared to properly treat patients through systematic research and detailed protocols. Secondly, to increase the representativeness of the sample, public recruitment will be carried out through posters, social platforms and other forms. Third, to improve the accuracy of the exercise, 8-form Tai Chi is adopted for the elderly, which is easy to understand and beneficial for physical conditions without excessive stress on the joints. Participants will be instructed by Tai Chi instructor with extensive experience and reminded of the forms by pre-recorded videos. Fourth, to achieve patient compliance and minimal follow-up loss, We have successful recruitment experience in our previous research with KOA with a low dropout rate. We will use the following strategies. Clinical trial publicity materials are distributed to all researchers to popularize clinical trial knowledge. Before assigning informed consent, participants should be explained in detail what to look for, including intervention requirements, timelines, positive impacts, and potential adverse events. In addition, we will strengthen KOA medical education, care for patients, and improve the overall quality of life of patients. Participants will receive an adequate transportation allowance if they complete all treatment and follow-up. More importantly, more flexible methods will be used to measure patients during follow-up, such as telephone questions or electronic CRF production through information or other communication software.

TC is easy to learn and self-administered and is not limited by time or space. If TC can improve clinical symptoms in KOA patients, we should promote it in the community in the future. The findings will help determine whether TC is superior to regarding effects on knee pain, physical function and muscle weakness in people with KOA and explore its correlation between pain intensity and muscle strength.

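### Last observation carried forward is fixed as the missing-data method at an expected 20% dropout, although the planned mixed model needs no imputation and LOCF can bias the week-12 comparison

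*Protocol article*

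**What the plan says.** The protocol article, under Data collection and statistical analysis, gives one method: "Missing data will be imputed through last observation carried forward (LOCF) methodology". The only other analysis it names is an auxiliary per-protocol set. The same section plans a linear mixed-effects model with group and visit as fixed effects for repeated outcomes.

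Under Sample size calculation it states: "considering the expected dropout rate of 20%, the study will require 100 patients in total".

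Under Study design and in Table 1, WOMAC is scheduled at baseline, week 6, week 12 and week 18. Isokinetic strength is measured "at baseline and week 12" (Measures of muscle strength), and Table 1 gives gait analysis the same two visits.

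The full analysis set requires at least one intervention and one outcome assessment. The text does not say whether that assessment must come after baseline. A later sentence in the same section includes all randomised participants who receive an intervention.

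**The concern.** The primary endpoint is change in WOMAC pain from baseline to week 12. Only two earlier visits can stand in for a missing week-12 score:

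- Week 6, for someone lost between weeks 6 and 12. This assumes that nothing changes in the second half of the course.
- Baseline, for someone lost before week 6, if that person is in the analysis set. This assumes no change at all.

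For strength and gait, baseline is the only value available.

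The filled-in values are then analysed as if observed, so the analysis does not reflect the lost information. The step is also unnecessary. A likelihood-based mixed model uses incomplete visit sequences directly under missing at random, and filling the gaps first throws that property away. At stake are the size of the primary estimate, its stated precision and, in some dropout patterns, the type I error.

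**Working it through.** **Inputs from the article.** Difference: "a 118-point improvement in WOMAC pain subscale occurred in the Tai Chi group compared to the attention control group". Design: "A sample size of 40 per group provides 90% power to detect these differences using a 2-sided significance level of 0.05". Dropout 20%, allocation 1:1, visits as above.

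**Assumptions, because the article gives no figure.** The share of the effect reached by week 6 (f), the share of dropouts lost after week 6 (s), any control-arm change, the split of dropout between arms, and the SD.

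**The plan's own figure.** 2 × 40 = 80, and 80/(1 − 0.20) = 100. The total is reproduced. No SD is stated, so the 40 per group cannot be checked; solving back gives an SD of about 161 (t test) to 163 (normal approximation).

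**Equal 20% dropout, all of it before week 12.** LOCF targets 118 × [0.8 + 0.2 × s × f].

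- s = 0.5, f = 0.5: 118 × 0.85 = 100.3, or 15% too small.
- s = 0 or f = 0: 118 × 0.80 = 94.4, or 20% too small.
- s = 1 and f = 1: 118, no bias.
- Central case with patients lost before week 6 left out of the analysis set: (0.8 × 118 + 0.1 × 59)/0.9 = 111.4, or about 6% too small.

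**Strength and gait.** With a fraction d missing at week 12, dropout unrelated to outcome and all patients kept, LOCF targets (1 − d) times the effect. At d = 0.20 the shrinkage is 20%. It is less if some of the 20% is lost between weeks 12 and 18. If patients lost before week 6 (half the dropouts) leave the analysis set, the factor is 0.8/0.9 = 0.89.

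**Unequal dropout with improving controls.**

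- No true effect, both arms improve 40 points, early dropout 10% versus 30%: 0.9 × 40 − 0.7 × 40 = 8 spurious points, favouring the arm with less dropout.
- True difference 118, controls improve 20 points by week 6 and 40 by week 12, dropout 30% in Tai Chi and 10% in control, half early. Tai Chi: 0.70 × 158 + 0.15 × 79 = 122.45. Control: 0.90 × 40 + 0.05 × 20 = 37. Difference: 85.5.
- Same, but controls improve 100 points (half by week 6) and dropout is 10% in Tai Chi and 30% in control: 0.925 × 218 − 0.775 × 100 = 124, larger than the truth.

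**Simulation.** 4,000 trials, 50 per arm, ANCOVA on the LOCF data against a likelihood estimate without imputation. Assumed: SD of change about 161, half of the change and half of the dropout before week 6, correlations 0.5 with baseline and 0.7 between weeks 6 and 12.

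- Equal 20% dropout at random: LOCF 100.2, likelihood 117.6. The model SE after LOCF is 28.0, against a sampling SE of 31.1 for the likelihood estimate, so about 10% smaller.
- Across all scenarios the LOCF model SE was 27.6 to 31.4, against 30.4 to 31.3.
- No true effect, both arms improving 100 points, dropout 30% and 10% either way round: the type I error was 0.076 to 0.085 with dropout at random and about 0.10 when poor responders left. With equal dropout it was 0.05 or below.
- The likelihood estimate stayed within about 1 point of the truth throughout.

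**The case against.** Several arguments on the other side are fair.

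- **The bias is conservative in the one case the article supports.** It gives a single 20% rate. With equal dropout the effect shrinks towards zero and the type I error is not raised. At an SD of about 161, 50 per arm and an effect of 100, power is still about 0.88 against the planned 0.90. This stands, and it limits the harm in that case. It does not make the estimate right.
- **Early dropouts may not be in the analysis set.** This stands; it moves the central case from 100 to 111.
- **The standard error is not wrong in itself.** With dropout at random, the model SE after LOCF (28.0) matches the spread of the LOCF estimate (28.4). It is too small only relative to an analysis that reflects the lost information.
- **The true value for people who stop is a choice of estimand.** Treating 118 as the truth assumes that dropouts would have fared like comparable completers. This stands, but LOCF does not target a clear alternative: it mixes zero change with half-course change according to when each person left.

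A reader might go further in two ways that the article does not support. One is that pain is bound to fall in both arms, so LOCF will create a false difference. The article states no control-arm change, describes the control programme as not meant to affect the main outcomes, and gives no reason for a particular dropout imbalance. The other starts from "Participants will receive an adequate transportation allowance if they complete all treatment and follow-up" and infers that the allowance itself produces the missing data. That is speculation. The same section offers telephone and electronic follow-up and reports low dropout in previous work, and the pain scale is self-administered.

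**Conclusion.** The point holds. The article fixes LOCF as its missing-data method beside a model that does not need it, so this is a stated choice and not a detail left to an unseen analysis plan.

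Under equal 20% dropout and a true difference of 118, LOCF targets about 100 points in the central case, about 111 if patients without post-baseline data are excluded, and 94 to 118 across timing assumptions. For strength and gait, 20% shrinkage is an upper case and not an exact figure.

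Bias in either direction and a raised type I error need both unequal dropout and improving controls. Neither is stated in the article, so the 8-point null example and the simulated error rates show what is possible and predict nothing. The sample size of 100 is not in question here.

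**What to change.** - Remove LOCF from the primary analysis. Fit the planned linear mixed model by REML to all observed visits under missing at random, include a group-by-visit term, and take the week-12 contrast as the primary result.
- Analyse strength and gait, which have one post-baseline visit, by observed-data ANCOVA adjusted for baseline, or by multiple imputation.
- State whether the outcome assessment required for the full analysis set must be post-baseline, and reconcile this with the sentence that includes all randomised participants who receive an intervention.
- If LOCF is kept at all, label it a sensitivity analysis.

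The cost is revised wording and a few model runs. The standard error will be slightly larger (about 31 against 28 points in the simulated central case), because it will reflect the information actually lost.
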